## Abstract

**Background:**

Chronic treatment of hypertension or heart failure very often includes an angiotensin-converting enzyme inhibitors (ACE-Is) or angiotensin receptor blockers (ARBs) as renin-angiotensin system inhibitors (RASi) treatments. To stop or not to stop these medications before major surgery remains an unresolved issue. The lack of evidence leads to conflicting guidelines with respect to RASi management before major surgery. The purpose of this study is to evaluate the impact of a strategy of RASi continuation or discontinuation on perioperative complications in patients undergoing major non-cardiac surgery.

**Methods:**

This is a multicenter, open-labeled randomized controlled trial in > 30 French centers. In the experimental group, RASi will be continued while the treatment will be stopped 48 h before the surgery in the control arm. The primary endpoint is a composite endpoint of major complications after surgery. An endpoint adjudication committee will review clinical data and adjudicate efficacy endpoints while blinded to the assigned study drug group. Main analysis will be by intention-to-treat comparing the composite outcome measure at 28 days in the two groups. A total of 2222 patients are planned to detect an absolute complications difference of 5%.

**Discussion:**

The results of the trial should provide robust evidence to anesthesiologists and surgeons regarding management of RASi before major non-cardiac surgery.

**Trial registration:**

ClinicalTrials.gov, NCT03374449. Registered on 11 December 2017.

**Electronic supplementary material:**

The online version of this article (10.1186/s13063-019-3247-1) contains supplementary material, which is available to authorized users.

## Background

More than 200 million major surgical procedures are performed annually worldwide. Many of these patients have co-morbidities including hypertension and/or heart failure [1, 2]. Chronic treatment of hypertension and/or heart failure very often includes a renin-angiotensin system inhibitor (RASi, angiotensin-converting enzyme inhibitors [ACE-Is] or angiotensin receptor blockers [ARBs]. To stop or not to stop these medications before major surgery remain an unresolved issue [3–7]. It is most likely that the strategy regarding management of RASi in the perioperative setting has an important impact on perioperative complications [8–10].

The lack of evidence leads to conflicting guidelines with respect to RASi management before major surgery. While French guidelines are to stop RASi patients with hypertension to avoid profound anesthetic-drugs-induced hypotension, international guidelines differ. The American Heart Association task force states that continuation of RASi perioperatively is reasonable (class IIa recommendation, level of evidence: B). They also recommend that if RASi therapy is withheld, it should be restarted as soon as feasible (level: C) [11]. These recommendations are based on few data suggesting an increased risk of overall complication after RASi discontinuation [12, 13] in the perioperative setting, while intraoperative hypotension can be managed with available vasoactive drugs during anesthesia [14]. The RAS acts on the vascular function and promotes thrombosis [15–17]. Modulating the RAS is therefore likely to impact global outcome after major surgery. The purpose of this study is to evaluate the impact of a strategy of RASi (i.e. ACE-Is or angiotensin receptor antagonists) continuation or discontinuation on perioperative complications in patients undergoing major non-cardiac surgery.

## Methods

### Design

The protocol was designed in accordance to the guidelines [18] (Fig. 1). This is a multicenter, open-labeled randomized controlled trial (RCT) in > 30 French centers. The randomization is performed at the CRU “Lariboisière-St Louis” and stratified by center and on the chronic heart failure status (New York Heart Association [NYHA] stage ≥ 2). The randomization list has been developed by a different biostatistician from the biostatistician who will conduct the final analysis within the CRU “Lariboisière- St Louis.” The list is inserted into the web-based software and then forwarded to the sponsor’s quality insurance team for validation. The patients are randomized on the day of written consent obtainment by web (CleanWeb) software, which assigns the patient a randomization number. Randomization is performed by blocks of four or eight with allocation concealment.

**Fig. 1 Fig1:**
[figure not shown]
SPIRIT schematic schedule of enrolment, interventions, and assessments

The randomization will be performed after the anesthesiology consultation and informed written consent has been obtained (Additional file 1). After randomization, a prescription indicating the treatment regimen in accordance to the arm in which the patient has been assigned will be edited automatically, printed, handed out, and explained to the patient. A phone call will be performed three days before surgery by a clinical study technician to ensure good understanding of the medication protocol (exact schedule of stopping of the chronic medication) and proper application to the protocol. In the experimental group, RASi will be continued, including on the day of the surgery, while the treatment will be stopped 48 h before surgery in the control arm (Fig. 2). Stopping the treatment 48 h before the surgery was proposed to avoid any remnant effect on the RAS blockage after stopping the treatments [19]. All patients will receive a leaflet in which they will record the discontinuation or continuation of the RASi. In this leaflet, the patients of the group: continuation of the RASi will report the adhesion to the protocol (i.e. treatment intake). The information collected in the leaflet will be add to the patients’ medical records and then collected by the clinical research assistant. We suggest the treatment will be resumed as soon as possible based on postoperative hemodynamic and renal status and availability of enteral route after surgery. The date of re-institution is indeed being collected. Patients having combined general anesthesia together with neuraxial anesthesia or peripheral nerve block could be enrolled.

**Fig. 2 Fig2:**
[figure not shown]
*Scheme* of drug intake according to the treatment arm (experimental arm with continuation of the treatment or control arm with withholding of the drug 28 h before surgery). Profiles A, B, and C refer to the number of drug intakes across a day

#### Inclusion criteria

Inclusion criteria were as follows: patients requiring major surgery defined as a surgery with an expected duration of > 2 h from the surgical incision and a postoperative hospital stay of least three days [20, 21]; age ≥ 18 years; signed informed consent; chronically treated (> 3 months before surgery) with RASi; and women of childbearing potential must agree to use adequate contraception.

#### Exclusion criteria

Exclusion criteria were as follows: emergency surgery (surgical treatment needed within 48 h); hyperkalemia (serum potassium level > 5.5 mmol/L) at the time of the anesthesiology consultation; patients for which death is deemed imminent and inevitable or patients with an underlying disease process with a life expectancy of < 1 month; patients with severe chronic renal insufficiency as defined by estimated glomerular filtration rate < 15 mL/min/1.73 m^2^ or requiring renal replacement therapy; patient with preoperative shock (defined by the need for vasoactive drugs before surgery); and lack of social insurance.

### Main objective and primary endpoint

The main objective is to evaluate the impact of RASi continuation or withholding on postoperative complications in patients undergoing major non-cardiac surgery.

The primary endpoint is a composite endpoint of all-cause mortality and major postoperative complications within 28 days after surgery, defined as one or more of the following:death;postoperative cardiovascular events (acute myocardial infarction, arterial or venous thrombosis, stroke, acute pulmonary edema, postoperative cardiogenic shock, acute severe hypertension crisis, severe cardiac arrhythmia requiring therapeutic intervention [22]);postoperative episodes of sepsis;postoperative respiratory complication (defined by the need for re-intubation and/or non-invasive ventilation for respiratory failure);unplanned intensive care unit admission or readmission;acute kidney injury (based on the serum creatinine item of the KDIGO criteria, baseline serum creatinine is preoperative value) and/or hyperkalemia (serum potassium level > 5.5. mmol/L requiring intravenous therapeutic intervention); andsurgical complication (need for reoperation for any reason and radiologic interventions for abscess drainage).

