In the case of lost-to-follow-up, the investigator will do his or her best to contact him or her in order to know whether he is alive. Mailing address, phone number, and phone number of at least one relative will be collected at inclusion to contact the patient. If an individual leaves the research prematurely, data relating to the participant can be used unless an objection was recorded when the patient signed the consent form. If consent is withdrawn, no data about the individual may be used unless he/she states in writing that he/she does not object. In practice, the participant is excluded from the research (Fig. 3 and Additional file 2).

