### Description of statistical methods

Main analysis will be by intention-to-treat comparing the composite outcome measure at 28 days in the two groups by chi-squared test (or Fisher’s exact test as appropriate). Based on an incidence of 25% of the primary endpoint in the reference group, a total of 2222 patients will allow a 80% power to detect a 20% relative decrease of complications in the experimental group (corresponding to an absolute decrease of incidence of the primary endpoint of 5%) using a Chi-square test and considering that the two interim analyses will lead to a final test at a nominal alpha value of 0.0465 according to the O’Brien and Fleming principle. More detailed statistical analysis can be found in the Additional file 2. Sample size calculation was performed using the nQuery Sample Size Software (Statistical Solutions Ltd., Cork, Ireland), statistical analysis will be performed using SAS 9.4 (SAS Institute Inc., Cary, NC, USA).

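### The primary endpoint opens at surgery although the arms diverge up to 48 h before it, so harms of stopping RASi before incision fall outside the primary comparison

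*Protocol article*

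**What the plan says.** All references are to the protocol article.

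- **Randomization (Methods, Design, and the text under Fig. 1).** It takes place before surgery, on the day of consent: "The randomization will be performed after the anesthesiology consultation and informed written consent has been obtained". A technician telephones the patient three days before surgery to check that the medication instructions are understood.
- **Start of the contrast (same text).** The continuation arm takes its treatment up to and including the day of surgery. The control arm stops 48 h before surgery. The Fig. 2 legend gives 28 h instead. The two places must be reconciled, but the point below holds with either.
- **Primary endpoint (Main objective and primary endpoint).** A "composite endpoint of all-cause mortality and major postoperative complications within 28 days after surgery". The components include death, stroke, acute pulmonary edema and acute severe hypertension crisis.
- **Secondary mortality (Secondary objectives and secondary endpoints).** The objective is mortality after surgery, but the endpoint is all-cause mortality 28 days from randomization. Hospital-free days in the same list run from surgery.
- **Analysis and size (Description of statistical methods).** Intention-to-treat, chi-squared test. The control rate is taken as 25%. On that basis the article states that "a total of 2222 patients will allow a 80% power to detect a 20% relative decrease of complications in the experimental group". The final nominal alpha is 0.0465. Further detail is left to Additional file 2, which is not shown.

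**The concern.** The Abstract and Background say that the trial evaluates a strategy of continuing or discontinuing RASi and its effect on perioperative complications. The strategy starts to act when the control arm stops treatment, but the endpoint starts to count only at surgery.

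In the interval between, the continuation arm stays on its usual treatment and the control arm does not. Any early harm of stopping would arise in the control arm alone and would not be scored. Several of the events one would look for there are already components of the composite once surgery has taken place. The same stroke counts if it occurs the day after the operation and does not count if it occurs the day before.

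Two consequences follow. The primary comparison can be tilted towards the control arm. And the primary endpoint and secondary mortality, both described as 28-day outcomes, count different deaths.

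**Working it through.** **1. Time windows side by side.** Let surgery be day 0 and randomization day −k. The article does not give k. The call three days before surgery implies that k is normally at least 3.

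| Event | Primary composite | Secondary mortality |
|---|---|---|
| Death between stopping and incision | not counted | counted, if within 28 days of randomization |
| Stroke, pulmonary edema or hypertensive crisis between stopping and incision | not counted | not applicable |
| Death on day d after surgery, d ≤ 28 − k | counted | counted |
| Death on day d after surgery, 28 − k < d ≤ 28 | counted | not counted |

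Secondary mortality therefore covers 28 − k days after surgery: 25 days for k = 3, 21 for k = 7, 14 for k = 14 and 7 for k = 21 (k assumed). An endpoint whose objective is mortality after surgery loses part of the postoperative period, and the lost part varies between patients with the waiting time.

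**2. The plan's own figure.** Inputs from Description of statistical methods: control rate 25%; "corresponding to an absolute decrease of incidence of the primary endpoint of 5" points, hence 20% in the experimental arm; alpha 0.0465. Assumed, because not stated: two-sided test and 1:1 allocation, hence 1111 per arm.

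Power = Φ{ [ |p1 − p2| − z·√(2·p̄(1 − p̄)/n) ] / √( [p1(1 − p1) + p2(1 − p2)]/n ) }, with p̄ = 0.225 and z = 1.991.

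- √(2 × 0.225 × 0.775 / 1111) = 0.01772; times 1.991 = 0.03527.
- √((0.1875 + 0.1600) / 1111) = 0.01769.
- (0.05 − 0.03527) / 0.01769 = 0.83, so power = 79.8%.

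The sample size formula for exactly 80% gives 1118 per arm, 2236 in total, 0.6% above 2222. The stated figure reproduces.

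**3. How large the omission could be.** No pre-surgery event rate is given, so a range is assumed. With an excess of 0.5% in controls, 0.005 × 1111 = 5.6 patients, and 0.5/5 = 10% of the target difference. With 1%, 11.1 patients and 20%.

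**4. Effect on power of counting these events.** The 25% is defined for the endpoint as written, that is, after surgery. Leaving pre-surgery events out therefore keeps power at 79.8%. Counting them adds to the control rate. The same formula gives:

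- 25.5% against 20%: 86.5%
- 26% against 20%: 91.5%

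These are upper figures. They assume no such events in the continuation arm and none in patients who later have a postoperative event anyway.

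**5. The opposite case.** If pre-surgery events are equally frequent in both arms, the longer window only adds noise: 25.5% against 20.5% gives 79.1%, and 26% against 21% gives 78.5%. The dilution is at most about 1 point over this range.

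**The case against.** **The window matches the stated objective.** The main objective speaks of postoperative complications in patients undergoing surgery, and some components, such as reoperation and re-intubation, have no meaning before it. This stands in part: an after-surgery window is a legitimate choice and the article is open about it. It does not meet the broader purpose in the Abstract and Background, and it does not answer the point that the intervention begins before the window opens.

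**Pre-surgery harms are not wholly lost.** Deaths before surgery count in secondary mortality if they occur within 28 days of randomization. That stands. Non-fatal events have no listed efficacy endpoint.

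**A reader might infer that patients not operated on drop out of the analysis.** The article does not say so. It names intention-to-treat and is silent on these patients; the rule may be in Additional file 2. As worded, the window has no starting date for them, but this is not evidence that they are removed. Nor does "In practice, the participant is excluded from the research" in Data management show it: that sentence concerns withdrawal of consent without a written statement of non-objection, and the text before it allows data of other early leavers to be used.

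**A reader might infer that the omission costs power,** by taking pre-surgery events out of the 25%. The 25% never contained them (step 4), so no loss follows from the plan's inputs.

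**The sample size has no reserve for missing outcomes.** That is so, but 2222 delivers its stated power for 2222 evaluable patients, so this is no error. With an assumed 5% lost, n = 1111 × 0.95 = 1055 per arm and power is 77.7%. If the same 5% are kept as non-events (23.75% against 19%, 1111 per arm), it is 77.1%.

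**Conclusion.** The concern holds as a mismatch between the start of the intervention and the start of the primary endpoint. Harms of stopping treatment that occur before incision are outside the primary comparison, and because only the control arm's treatment changes then, the omission can favour that arm. Its size cannot be taken from the article. Over an assumed excess of 0.5% to 1% it would be 10% to 20% of the target difference. With an interval of at most two days by the text, the true figure is probably at or below the lower end.

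The different time origins of the primary endpoint and secondary mortality are a plain inconsistency in the text and need no assumption.

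The documents do not support going further. They do not show that non-operated patients are excluded, that planned power is reduced, or that the sample size is miscalculated. The power figures rest on a two-sided test and 1:1 allocation, neither of which is stated.

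**What to change.** 1. In both arms, count death and the applicable medical components from randomization, or from the protocol's stopping time before scheduled surgery (48 h in the text), to 28 days after the **actual** surgery. Components that presuppose an operation start at surgery.
2. Use the scheduled date as day 0 only for patients never operated on, and keep them in the intention-to-treat analysis. It should not be used for postponed operations: with a three-week delay, 28 − 21 = 7 days of postoperative follow-up would remain.
3. Give all-cause mortality the same start and end.
4. Report pre-surgery events and cancelled operations by arm, cancellations with their reason. Keep the after-surgery-only composite as a sensitivity analysis.
5. Optionally, state that the 80% refers to 2222 evaluable patients, about 78% if 5% have no outcome (assumed rate).

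**Cost:** wording of the endpoint and the eCRF, and short follow-up of the few patients not operated on. If pre-surgery events turn out equally frequent in both arms, there is a slight dilution, about 1 point of power at an assumed 1%. Starting at the stopping time rather than at randomization limits this dilution, because it leaves out days on which both arms are treated alike. No extra recruitment is needed.

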### Description of parameters for assessing efficacy endpoints

The primary endpoint is a composite endpoint, which will be collected at each visit. Diagnosis of complications will be made by investigators (anesthesiologists for medical complications and surgeons for surgical complications) and/or a specialist if he or she has been consulted for a complication. Because a double-blinded trial was not feasible (i.e. due to the higher number of medications containing an ACEi or ARB), an endpoint adjudication committee will review all events. Research assistants and experts of the adjudication committee will be blinded to the group assignment. Clinicians in charge of the patients will not be blinded. The endpoint adjudication committee will review clinical data and adjudicate efficacy endpoints while blinded to the assigned study drug group. The adjudication committee will be composed of physicians (cardiologists, neurologists, nephrologists, anesthesiologists) not participating into the study as investigators who will be provided with available collected data during the conduct of the study.

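### The surgical component of the primary endpoint does not separate planned from unplanned reoperation, so a staged return to theatre can count as a major complication

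*Protocol article*

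**What the plan says.** Under *Main objective and primary endpoint*, the protocol article defines the primary endpoint as a "composite endpoint of all-cause mortality and major postoperative complications within 28 days after surgery", met by one or more listed items. The surgical item is headed as a surgical complication and spelled out in brackets as "need for reoperation for any reason and radiologic interventions for abscess drainage". The ICU item in the same list is "unplanned intensive care unit admission or readmission".

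Under *Description of parameters for assessing efficacy endpoints*, complications are diagnosed by investigators ("anesthesiologists for medical complications and surgeons for surgical complications"), and then "an endpoint adjudication committee will review all events", blinded to group. No rule for planned returns is given there, and the committee's listed specialties do not include surgery: "The adjudication committee will be composed of physicians (cardiologists, neurologists, nephrologists, anesthesiologists".

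*Description of statistical methods* sets the sample size: "Based on an incidence of 25% of the primary endpoint in the reference group", and "a total of 2222 patients will allow a 80% power to detect a 20% relative decrease of complications in the experimental group". The difference is 5 percentage points, and the final test uses a nominal alpha of 0.0465.

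**The concern.** The composite is meant to capture major postoperative complications, yet the bracketed rule tells the reader not to ask why the patient went back to theatre. Consider a patient with an uneventful course whose second stage was fixed at the consultation and done on day 14. The bracket makes this patient an event; the heading suggests otherwise. The authors drew the planned/unplanned line for ICU admission but not here, so the text does not settle which reading applies. With more than 30 centres, that invites inconsistent coding of the primary endpoint.

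Eligibility leaves room for such patients. It rests on expected duration and length of stay, and it excludes emergency surgery but not staged procedures.

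A return scheduled before randomization cannot be changed by continuing or stopping RASi. If such returns count, they add events to both arms that carry no information about treatment. They can shrink the observed difference, and they raise the reported complication rate.

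**Working it through.** **Inputs from the article.** Control rate 25%, experimental rate 20%, total 2222, final alpha 0.0465.

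**Assumptions.** Allocation is 1:1 (1111 per arm) and the test is two-sided; the article states neither. The planned-return rate q is also assumed, because the article gives none. It is taken as equal in both arms and independent of true complications.

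**Formula.** Normal approximation to the chi-squared test, with p̄ = (p1 + p2)/2:

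power = Φ{ [(p1 − p2)√n − z√(2p̄(1 − p̄))] / √(p1(1 − p1) + p2(1 − p2)) }, with z = 1.991 for alpha 0.0465.

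**Step 1: reproduce the plan.** With p1 = 0.25, p2 = 0.20 and n = 1111:
- (p1 − p2)√n = 0.05 × 33.33 = 1.667
- z√(2 × 0.225 × 0.775) = 1.176
- √(0.1875 + 0.16) = 0.589
- power = Φ[(1.667 − 1.176)/0.589] = Φ(0.833) = 79.8%

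Solving for 80% power gives 1118 per arm, or 2236 in total, 0.6% above the stated 2222. The stated design reproduces.

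**Step 2: add planned returns under three readings of the 25%.**

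*A. The 25% and 20% describe true complications, and planned returns come on top.* Then p1 = 0.25 + 0.75q and p2 = 0.20 + 0.80q.

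*B. The 25% already contains planned returns, and the 20% relative reduction acts only on true complications.* Then p1 = 0.25 and p2 = q + 0.80(0.25 − q).

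*C. The 25% and the 5-point difference describe the endpoint exactly as written.* Nothing changes.

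| Assumed q | A: p1 v p2 | A: power | A: N for 80% | B: p1 v p2 | B: power | C: power |
|---|---|---|---|---|---|---|
| 0.5% | 25.4% v 20.4% | 78.9% | 2286 | 25% v 20.1% | 78.1% | 79.8% |
| 1% | 25.75% v 20.8% | 78.0% | 2338 | 25% v 20.2% | 76.3% | 79.8% |
| 2% | 26.5% v 21.6% | 76.2% | 2440 | 25% v 20.4% | 72.5% | 79.8% |

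Worked case, A at q = 2%: p1 − p2 = 0.265 − 0.216 = 0.049. Power = Φ[(1.633 − 1.203)/0.603] = Φ(0.713) = 76.2%. The relative reduction falls from 20% to 0.049/0.265 = 18.5%.

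Patients counted only because of a planned return, in A at q = 2%: 1111 × 0.02 × 0.75 = 16.7 in the control arm and 1111 × 0.02 × 0.80 = 17.8 in the experimental arm.

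Power falls to 78% at q of about 1.0% under A and about 0.5% under B.

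**The case against.** The strongest reply is contextual. The bracket sits under a heading that names a surgical complication, inside a list of major complications. A second stage booked in advance is not a complication, nor a need that arises after the index operation. A surgeon has to diagnose a complication before anything reaches the committee. A cause-blind rule also has a purpose in an open-label trial, since it limits argument about attribution. And the article condenses a fuller protocol, so detailed event rules may sit elsewhere.

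Much of this stands. It shows that planned returns need not count, and a reader who infers that they certainly will goes beyond the text. It does not show that they are excluded. The bracket is the working definition and is cause-blind, while the neighbouring ICU item shows that the authors knew how to write the restriction. Blinded review guards against differential coding by arm; it does not tell the committee which reading to use.

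A reader might also infer that the trial has less than its stated 80% power. The article does not support that. It gives 25% as the incidence of the primary endpoint itself, and the 5-point difference likewise, so reading C is the most literal. Readings A and B each need a further assumption about what the 25% contains, plus a value of q that has no source in the article.

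Finally, the bracket joins reoperation and drainage with *and*, where other items use *and/or*. One could infer that drainage alone does not count. That is plainly not intended; it is a drafting matter, to be tidied in the same edit.

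**Conclusion.** The wording defect stands: the surgical item leaves open whether a return to theatre planned before randomization is a primary-endpoint event, and its literal wording says it is. The consequence is possible dilution, an inflated complication rate and uneven coding between centres. It is not bias towards either arm, because a plan fixed before randomization is unrelated to allocation.

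The effect on power is conditional. It is nil under reading C, and about 1 to 4 points under A or 2 to 7 points under B for assumed q between 0.5% and 2%. These figures rest on 1:1 allocation, a two-sided test, equal q in both arms and independence from true complications. The sample-size calculation itself is sound. This is a cheap improvement to a stated rule, not an error that undermines the design.

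**What to change.** Reword the item to: *surgical complication (unplanned reoperation, i.e. not part of the surgical plan recorded before randomization, and/or radiologic intervention for abscess drainage)*. Have the blinded committee apply this against the pre-randomization plan. Report the result counting all reoperations as a sensitivity analysis. State whether the 25% control rate was derived under the same definition.

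The cost is one sentence in the endpoint definition and in the adjudication rules, one yes/no field for a planned second stage completed before randomization, and one classification per reoperation. The event count may fall slightly. No extra patients or procedures are needed.
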